# Ethical considerations and risk and burden

As with all research involving human subjects the wellbeing and safeguarding of individuals is paramount.

All researchers who have direct contact with participants will have all of the necessary approvals in place to include research passport, health checks, employment contracts, disclosure and barring service checks and will be fully trained to undertake the examinations included within the study.

Interview and other data (e.g. bioelectrical impedance, dietary intake) will be pseudonymised using a unique identifier at the time of collection. For long term storage and analysis, pseudonymised data will be encrypted and compressed, and retrievable only by members of the core research team. All anonymised data will be securely stored within a fire-walled password protected domain. Only core team member responsible for data analysis can link pseudonymised data back to individual participants.

As stated above, this study will exclude individuals who do not have capacity to consent. Should an individual lose consent during the ‘active’ period of this study then the participant will be withdrawn at that point. Permission to retain data gathered before loss of capacity is included in the participant consent form.

It is very unlikely that participants will experience harm by taking part in this study. There is small risk of increased muscle soreness and discomfort after each exercise session that will be carefully monitored and recorded by a trained exercise physiologist. Participants will be assessed regularly for muscle soreness and any signs of excess discomfort and stress using visual analogues scale, and will be called at home after each intervention session in the evening (i.e. twice a week over 6 weeks of intervention). Muscle injury with the proposed RE programme is highly unlikely because each participant will exercise at the sub-maximal level of effort, and will be supervised by a trained and certified exercise physiologist. The Parks (Contours gym) has health and safety procedures and indemnity insurance covered through the gym membership in the case of adverse events related to the equipment and facility use (contact person: [name], Operational Manager, Indoor Sport and Leisure, North Tyneside Council; [[contact]](mailto:[contact]) ). Any change in blood pressure and heart rate pre and post-RE will be carefully monitored and recorded.

There is also a small risk of gastrointestinal discomfort and possible unknown milk allergies (lactose or milk proteins). Participants who report any significant discomfort associated with milk or control drink intake (e.g. nausea, indigestion, diarrhoea, etc.) will be excluded from the study. In addition, there is a small risk of metabolic changes and weight gain due to the consumption of 650 kcal from whole milk and control drink (2 × week over 6 weeks) which will be counteracted by the increased energy expenditure during the RE programme. Appetite will be assessed at baseline and post-intervention, and total energy intake will be estimated using the Intake24 (computerised 24-hr dietary recall) pre- and post-intervention to examine any changes in energy intake. Also, weight and body fatness will be estimated using the Tanita Body Composition Analyzer at baseline and after the intervention.

There is also a small risk of falling during the walking test. However, the attending researcher will assess individual risk at the point of data collection (re-check exclusion criteria and endurance of consent) and omit measurements/ test if they felt it unsafe or that capacity to consent is not present or consent does not endure. It is made clear to participants that they are free to withdraw at any time. Should a decision to withdraw from the study be made, a reason for the withdrawal will be recorded. However, participants can withdraw without providing any explanation.

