7. Muscle strength: maximum grip strength measured 3 times in each arm
8. Physical performance: Short Physical Performance Battery^26^ (balance, 4m-gait speed, 5-chair stands)
9. Muscle mass (body composition), as measured by Bioelectric Impedance Analysis (BIA; Tanita MC-780MA Body Composition Analyzer).

Baseline assessments of blood pressure and muscle mass (body composition) will be conducted at the intervention site (The Parks, Contours gym) before the first RE session, and dietary intake and appetite will be assessed during the post-exercise recovery period. Body analyser will be parts tested by the NTGH.

Detailed health and functioning profile will involve minimal risk and inconvenience to participants and will be conducted under 70 minutes (including verification of the informed consent and excluding assessments done at The Parks).

- INTERVENTION: MILK/ CONTROL DRINK + RESISTANCE EXERCISE (main team member(s) responsible: certified exercised physiologist and [name])

Thirty participants will be randomized into three groups (10 each; 5 men and 5 women):

1. ‘whole milk + RE’;
2. ‘skimmed milk + RE’, and
3. ‘control drink’ (juice supplemented with carbohydrates) + RE’.

Resistance exercise programme

RE will be conducted over 6 weeks (twice a week on two non-consecutive days) at The Parks, Contours gym & fitness suite, North Shields, North Tyneside Council in a small group of 2-3 participants, and will be supervised by a trained and experienced exercise physiologist. Participants will be advised to resume their usual diet, and to have their regular breakfast before the intervention. Four sets of 8-12 repetitions (upper and lower body) exercises at the sub-maximal level of effort (70-79% 1-repetition maximum) will be performed after a short warm-up exercise (e.g. 5 minutes of stretching exercises, walking or stationary cycling)^36,37^. Each set of RE will be followed by 1-2 minute of resting period, and a rest of 4 seconds between repetitions^36^. Each participant will receive a booklet with diagrams and short instructions of exercise programme (RE booklet). To increase their engagement in exercise, each participant will have the opportunity to record in the RE booklet how many repetitions and how much weight for each set of exercise they have completed and lifted.

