Exercise intensity, volume, frequency and duration have been determined based on the recent literature^36-38^, and the American College of Sports Medicine (ACSM) recommendations for older adults^37^. Details about the RE programme over 6 weeks are outlined in the RE protocol (MIlkMAN_Resistance Exercise Protocol_v.1-20-07-18). The complete RE session will be finalised within 1 hour, except the first RE session, which will last 1 hour and 30 to 40 minutes and include a short induction programme at the gym detailed below. Blood pressure and heart rate will be measured pre and post each RE session. Blood pressure classification and cut-offs for the blood pressure change pre and post-RE will be based on the guidelines provided by the American College of Cardiology/American Heart Association Task Force^39^ and on the published literature^40-42^. For older adults aged 65 and over blood pressure of 130/80 mmHg is considered as optimal^39^. Exercise physiologist will record changes in blood pressure and heart rate pre and post each RE session. If participant’s blood pressure approaches the exclusion criteria for the study (>160/100 mmHg for hypertension and <100mmHg systolic for hypotension) before exercise, the Chief Investigator (a consultant physician) will be notified and consulted. Changes that are regarded to be adverse events will be recorded and reported to the Chief Investigator ([name]) for evaluation and further adverse events reporting (described below). Any other health risks will be closely monitored by exercise physiologist. Post-exercise differential ratings of perceived exertion (RPE) ~ 10 minutes after the completion of exercise will be assessed using the CR100® scale^43^ (Appendix 2). The scale offers finely graded numerical range of 0-100 arbitrary units (AU) with several verbal anchors next to the scale corresponding to whole numbers (0 ‘nothing at all’; 12 ‘easy’; 22 ‘moderate’; 35 ‘somewhat hard’; 50 ‘hard’; 70 ‘very hard’; 100 ‘maximal’). Participants will be asked to self-asses their level of perceived exertion for the overall session, and upper-body and lower-body muscles. Muscle soreness will be assessed with a simple visual analogue scale (Appendix 3) ~40-45 minutes after each RE session. Additionally, each participant will be called at home in the evening (up to 6-7 hours post-RE) to evaluate his/ her muscle soreness using the same visual analogue scale.

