Milk / control drink will be consumed as a bolus intake of 500ml under the supervision of a researcher immediately after exercise over 40-50 minutes during the recovery period (or longer if needed). Participants will be advised to resume their usual diet. Second dose of 500ml will be consumed at participants’ home over the next 4-5 hours. All drinks consumed at home will be clearly labelled as either ‘MIlkMAN study milk’ or ‘MIlkMAN study juice’. Second dose of 500ml can be consumed with other foods as a part of their usual diet (e.g. tea, cereal, mushed potatoes, etc.). Participants will be contacted by phone in the evening to check for muscle soreness and compliance with milk/ control drink consumption. Each participant will be provided with a plastic measuring jug (500ml) and a log sheet to measure and record milk/control drink consumption at home and to report it back to a researcher conducting the phone call.

On average, 500ml milk contains ~20g of protein needed to stimulate muscle protein synthesis above stimulation provided by RE. Whole (cow) milk (nutritional estimates of 22 UK samples during winter and summer) provides 66 kcal/100g of energy^44^. Fresh milk will be provided by Arla® (Nutrition Specialist: [name] at Arla Foods). Arla Cravendale® whole milk contains 3.6g fat, 3.4g protein, and 4.7g of carbohydrates per 100g of milk. Arla Cravendale® skimmed milk contains 0.3g fat, 3.6g protein, and 4.9g of carbohydrate per 100g of milk. Energy of control drink (cranberry juice; Ocean Spray Classic) will be balanced to match whole milk energy content and supplemented with maltodextrin (e.g. cranberry juice (45kcal/100g of energy^44^) will be supplemented with 6.05g of maltodextrin (3.8kcal/g) per 100g of juice; 1tsp = 15kcal; 30.25g for 500ml of juice).

Milk and control drink storage and handling

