**Appendix 2**

R100® scale^43^

**Instructions for participants** (explained to participants by exercise physiologist)

*Assessment ~10 minutes after exercise*

- - Using the scale, we would like you to rate your perceptions of EFFORT, that is, how difficult the session felt to you.
  - Your perception of EFFORT should be a conscious awareness of how hard (or easy) the whole session was. It shouldn’t be influenced your feelings of fatigue, pain or discomfort (try separate these from effort as best you can).
  - You will be asked to rate your perceptions of overall effort, and then separate scores for upper-body muscle effort and lower-body muscle effort.
  - For upper-body muscle RPE, the perception of exertion depends mainly on the strain and exertion in your arm muscles during training.
  - For lower-body muscle RPE, the perception of exertion depends mainly on the strain and exertion in your leg muscles during training.
  - Your scores should reflect the whole session, which is all exercises that you completed after the warm-up.
  - Try to appraise your feelings as honestly, without thinking about what the actual training was or should have been.

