**Appendix 3**

Visual analogue scale for muscle soreness

[figure not shown]

0 = no pain, 1-3 = mild pain, 4-6 = moderate pain; 7-10 = severe pain

**Instructions for participants** (explained to participants by a researcher)

- This is a Visual Analogue Scale. The scale describes the intensity of your pain, 0 meaning no pain at all, 1 to 3 meaning mild pain, 4-6 moderate pain, and 7-10 the worst pain.
- Assessment ~45 minutes after exercise: Which number on the scale describes the best your muscle soreness in your (i) arms and (ii) legs?
- *Assessment in the evening over the phone (6-7 hours after exercise)*: A researcher will call you in the evening after each visit to the Parks to ask you again about your muscle soreness in your arms and legs. Please use the visual analogue scale that we gave you to rate your muscle soreness in your (i) arms and (ii) legs.

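### The safety section says the visual analogue scale covers discomfort and stress, but it asks only about arm and leg muscle soreness, and no post-session question asks about other pain

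*Protocol*

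**What the plan says.** In the Protocol, the section on ethical considerations, risk and burden describes the monitoring after exercise this way: "Participants will be assessed regularly for muscle soreness and any signs of excess discomfort and stress using visual analogues scale". The same sentence adds the evening call after each session. The sentence shortly before it says that the exercise physiologist will monitor and record soreness and discomfort after each session.

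The exercise programme text under Data collection gives the scale a narrower job: "Muscle soreness will be assessed with a simple visual analogue scale (Appendix 3"), at about 40-45 minutes after each session and again by phone in the evening. The text on milk and control drink intake describes that call: "Participants will be contacted by phone in the evening to check for muscle soreness and compliance with milk/ control drink consumption".

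Appendix 3 introduces the scale in general terms ("The scale describes the intensity of your pain") but then puts only two questions. After exercise: "Which number on the scale describes the best your muscle soreness in your (i) arms and (ii) legs"? In the evening: "Please use the visual analogue scale that we gave you to rate your muscle soreness in your (i) arms and (ii) legs".

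The adverse events section defines an adverse event broadly, including unfavourable symptoms, and requires all of them to be recorded on a case report form with description, duration and action taken. Adverse health effects, with muscle soreness as one example, are among the primary measures. Hypothesis 2 expects no adverse health effects, and names muscle damage and soreness among those it has in mind.

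**The concern.** The safety section credits one instrument with three tasks: soreness, excess discomfort and stress. The instrument performs only the first, and only for the muscles of the arms and legs. A participant with joint or back pain after loaded exercise can truthfully answer 0 for arms and 0 for legs at every contact, because neither question is about that pain.

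A statement that adverse effects were absent is only as strong as the questions asked. If nothing scheduled after a session asks about other pain, a low count may partly reflect the lack of a question. The study is meant to inform a larger trial, so an incomplete tolerability record would be carried forward into its planning.

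**Working it through.** No sample size, power or error rate is involved, so the check sets the texts side by side.

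**Step 1: what is promised and what is asked.**

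| Place in the Protocol | Content |
|---|---|
| Ethical considerations and risk and burden | Scale covers soreness, excess discomfort and stress |
| Data collection, exercise programme | Scale covers muscle soreness |
| Appendix 3, about 45 minutes after exercise | Muscle soreness: arms, legs |
| Appendix 3, evening call (6-7 hours after) | Muscle soreness: arms, legs |
| Data collection, milk and control drink intake | Evening call covers soreness and drink intake |

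The first row is wider than all the others. Neither question in Appendix 3 takes up the general pain wording of its introduction beyond the arm and leg muscles.

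**Step 2: how often the scale is used.** Inputs: 2 sessions a week, 6 weeks, 2 time points per session, 2 body sites, 30 participants, full attendance.

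- Sessions: 2 × 6 = 12 per participant.
- Rating contacts: 12 × 2 = 24 per participant; 24 × 30 = 720 in all.
- Ratings: 24 × 2 = 48 per participant; 48 × 30 = 1,440 in all.

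These counts show how much soreness data is planned and how many existing contacts could carry a further prompt. They do not measure how many symptoms are missed.

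**Step 3: other routes into the record.**

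- At the gym: the exercise physiologist monitors and records soreness and discomfort and watches for other health risks. Sessions have 2-3 participants, and a supervised recovery period follows. This is real capture, but without a stated question.
- At any time: adverse event recording is broad enough to include joint, back or chest pain once it is noticed or reported. The section states no prompt for eliciting it.
- At home: the evening call is the only scheduled same-day contact, and its stated content is soreness and drink intake.
- At the end of the study: participants say what they liked and disliked. That is an open route, but it comes after all sessions, and pain is not one of the listed themes.

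**Step 4: what remains.** Other pain can enter the record by observation or report while the participant is at the gym. After that, it depends on the participant raising it.

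**The case against.** The strongest reply is that a symptom without a rating is not a symptom without a record. The adverse event definition takes in such complaints, every event goes on a case report form, and the safety section itself has the physiologist record discomfort. The list of adverse effects among the primary measures is illustrative, so nothing confines the measure to the scale. All of this stands. It limits the point to how completely symptoms are elicited, chiefly after the participant goes home.

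The safety sentence might also be read loosely, with the scale attached to soreness alone. As written it attaches to all three items; if only soreness was meant, the sentence still needs correcting.

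Three stronger readings are tempting, and the document does not support them:

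- A reader might infer that a participant with back pain would be reported as free of harm. That does not follow, because a recorded adverse event would stand beside the zero soreness scores.
- A reader might infer that trunk soreness from the exercises is missed. The programme is described only as "Four sets of 8-12 repetitions (upper and lower body) exercises", and the details are in a separate exercise protocol that is not shown, so trunk loading cannot be established. Arms and legs may also serve as lay terms for upper and lower body, since Appendix 2 explains upper- and lower-body effort in those terms.
- A reader might fault the effort scale in Appendix 2 for telling participants to set pain and discomfort aside. That instruction keeps the effort rating specific, and the protocol does not offer that scale as a safety instrument.

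**Conclusion.** The mismatch is established from the text: the safety section claims more for the visual analogue scale than Appendix 3 measures, and no question scheduled after a session asks about other pain or discomfort. The consequence is possible under-ascertainment of adverse effects, which are a primary measure and the subject of Hypothesis 2.

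The size is modest and cannot be put as a number. The protocol gives no rate for such complaints, and any percentage would be a guess. No calculation is affected. The same questions are put to all three groups, so the point concerns the absolute level of recorded effects and does not by itself show bias between groups.

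The conclusion assumes that the evening call follows its stated content and that no unseen case report form or call script already contains a wider question. If one does, only the wording needs to be reconciled.

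**What to change.** At the two existing contacts, about 45 minutes after exercise and in the evening call, add one open prompt: *any other pain or discomfort since the session, and where?* Record positive answers through the adverse event process that the protocol already sets out. Report them separately from the arm and leg soreness scores. Merging them would blur a specific measure that is tied to the rationale for milk.

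Reword the sentence in the section on ethical considerations, risk and burden so that it claims arm and leg soreness for the scale and other pain or discomfort for the prompt. Bring the exercise programme text, the description of the evening call and Appendix 3 into line with it. If the prompt is not adopted, the sentence should still be narrowed to what the scale asks.

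The cost is one question and one case report form field at each of 24 contacts per participant (720 in all with full attendance), with no added visit or call. Somewhat more minor adverse events will be recorded, so the report should say that they were actively asked about.

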# Adverse events (defining, recording, reporting)

Recognising the importance of appropriately recording and reporting all Adverse Events (AE) which occur during the course of a participant’s involvement in MIlkMAN pilot study will be in accordance with National Research Committee (NRES) guidelines for non-CTIMP trials. A Decision Tree for Adverse Events Reporting for non-CTIMPs will be followed to classify ARs and their reporting (<https://www.nihr.ac.uk/our-faculty/clinical-research-staff/learning-and-development/documents/Decision%20Tree%20for%20Adverse%20Event%20Reporting%20NON%20CTIMPS.pdf>). We will use the latest Practice Guidelines Note <https://www.ntw.nhs.uk/content/uploads/2014/11/RGP-PGN-07-Safety-Reporting-V01-Iss-2-Nov-17.pdf> outlined by the Northumberland, Tyne and Wear NHS Foundation Trust policy as a template for the reporting of adverse events in non-CTIMPs.

This policy defines an AE as: any untoward medical occurrence in a study participant which does not necessarily have a causal relationship with the ‘treatment’ under study (e.g. abnormal laboratory findings, unfavourable symptoms or diseases). A Serious Adverse Event (SAE) is defined as: resulting in death, a life-threatening event, hospitalisation or prolongation of hospitalisation, a persistent or significant disability or incapacity, a congenital anomaly or birth defect, or is otherwise considered medically significant by the investigator.

All AE’s will be recorded on a case report form (CRF), the trial master file, and participants medical notes. Detailing: a description of the event, duration of AE (date(s)/times), and any actions taken.

In addition SAE’s will be reported to the study Chief Investigator ([name]) and the sponsor (Northumbria Healthcare NHS Foundation Trust, North Tyneside General Hospital) by contacting the sponsor’s main contact ([name]; [[contact]](mailto:[contact]); R&D at the NTGH) within 24 hours of becoming aware of the event. If the Chief Investigator ([name]) and senior co-investigators decide that the SAE is related to the study and unexpected then reports will be made to (i) the Newcastle Research Ethics Committee, using NHS HRA non-CTIMP safety report to REC form, within 15 days of becoming aware of the event and (ii) through the DATIX Incident Reporting System. If the event is assessed as a serious incident (SI), defined as resulting in unexpected or avoidable death, or serious harm, an R&D manager will inform the Director of Quality and Effectiveness, via the Clinical Governance and Risk Department (CGARD), as soon as possible by phone.

All SAEs involving a non-CE marked device under clinical investigation will be reported to the Medicines and Healthcare Products Regulatory Agency (MHRA) Devices Division, whether initially considered to be device related or not. SAEs involving CE-marked devices in a post-market surveillance study will be reported to the MHRA Adverse Incident Centre under the requirements of Devices Vigilance.

Any occurring SAEs will be included in the Annual Progress Report to the REC.

